### Randomization, stratification, and blinding

This is a randomized multicenter study. After giving informed consent and being enrolled in the study, patients will be randomized into different groups in the operating room after surgical exploration. The permuted-blocks randomization protocol will comprise five separate randomization lists, one for each participating hospital, and will be centrally managed by the Clinical Trial Center of the lead hospital, the Third Military Medical University. When an eligible case is enrolled, the Clinical Trial Center will be called and a randomization number will be assigned according to the designated list. Because there are two groups in this trial, the block sizes will be 4, 6, and 8 and will be randomly assigned. Patients will be stratified by site and randomized in a ratio of 1:1 into the two groups. Patients and outcome assessors will be blinded to achieve a minimum bias.

### Endpoints

The primary trial endpoint will be tumor recurrence diagnosed by enhanced CT scan or serum alpha-fetoprotein level. Secondary objectives are to examine overall survival, blood loss, duration of operation, requirement for blood transfusion, length of hospital stay, and morbidity rate. The formal end of the study will be at the end of the 3-year follow-up period of the last patient to be enrolled. All these parameters will be recorded prospectively as part of the study protocol. Final evaluation of the primary and secondary endpoints of the study will be performed 1 year after enrollment of the last patient.

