However, this possibility has been raised by the results of recent animal studies [33,34]. It has been shown that surgical stress, such as I/R injury, might cause delayed damage to the residual liver (“soil”), and may also affect the behavior of the tumor cells (“seeds”) by activating cell invasion and migration signal pathways, thus accelerating tumor recurrence. I/R injury tends to disrupt normal liver tissues and create an environment that may promote tumor recurrence. Hepatic resection will also induce tumor cells to become more aggressive by promoting the production of cytokines by nonparenchymal liver cells [35]. From the results of these studies, it can easily be concluded that I/R injury to the liver remnant may be a significant factor promoting tumor recurrence and metastasis in experimental animal models. Animal models may introduce potentially important concepts related to the mechanisms involved in tumor recurrence associated with surgical stress, specifically hepatic I/R injury. Furthermore, the promotion of liver metastasis by hepatic I/R injury during liver resection has been reported in colon cancer patients [36,37], and minimization of I/R injury can attenuate metastasis of colorectal cancer to the liver [38-40]. Liver transplant recipients with HCC who receive living-donor grafts experience a higher recurrence rate [41,42] due to the more severe acute-phase injury to the liver graft.

For primary liver cancer patient undergoing hepatectomy, the effects of I/R injury on tumor recurrence need to be determined. Because use of the Pringle maneuver during hepatic resection will lead to I/R injury to the liver remnant, we can rationally deduce that it may harm liver function, make the tumor cells more aggressive, and increase the likelihood of recurrence. If this is found to be true in humans, routine use of the Pringle maneuver should be re-evaluated. It is unfortunate that there are currently no reported data or randomized controlled studies examining this issue.

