### Our hypothesis

We hypothesize that the high incidence of tumor recurrence and the poor long-term prognosis of patients with HCC might be partly due to the I/R injury resulting from use of the Pringle maneuver during hepatectomy. If possible, this procedure should be avoided or revised when performing a hepatectomy on cancer patients [43]. In a clinical setting, many factors such as blood loss, blood transfusion, liver function, and HBV load affect the prognosis of cancer patients. These factors may each have different, and sometimes even opposing, effects on laboratory test results. However, evaluation of the effects of the Pringle maneuver remains an important and urgent issue in liver surgery, which may lead to a significant change to our current knowledge. We therefore designed a multicenter, prospective, randomized trial to test our hypothesis.

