### Follow-up

Patients who have completed the interventions will be included in the standard follow-up program. Follow-up visits will be at 1, 3, 6, 9, and 12 months and then every 6 months until 3 years after their operation. Each visit will include physical examination, tumor marker tests, liver function tests, chest x-ray, and ultrasound examination. In addition, enhanced CT scans of thorax and abdomen will be performed at 3, 6, 12, 18, 24, 32, and36 months postoperatively. Additional investigations including 18 F-fluorodexyglucose positron emission tomography scan, magnetic resonance imaging, or digital subtraction angiography will be scheduled as required to investigate possible tumor recurrence. At each visit, a follow-up evaluation form will be completed. If tumor recurs, the patient will be hospitalized and treated according to the clinical situation.

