### Duration of the trial, and current trial status

The trial is planned to last a total of 5 years, consisting of: protocol development (6 months), training (3 months), main recruitment (9 months), follow-up (36 months), and analysis (6 months). All the team members have completed their training. The expected end date of this trial will be July, 2013.

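### As worded, an alpha-fetoprotein level alone can count as the primary recurrence event; marker-only events that are not tumour would dilute the treatment effect, probably modestly

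*Protocol article*

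**What the plan says.** The Endpoints section gives the primary endpoint as "tumor recurrence diagnosed by enhanced CT scan or serum alpha-fetoprotein level". The two routes are alternatives.

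The Follow-up section sets visits at months 1, 3, 6, 9 and 12 and then every 6 months to 3 years, which makes nine visits (1, 3, 6, 9, 12, 18, 24, 30, 36). On their content it says: "Each visit will include physical examination, tumor marker tests, liver function tests, chest x-ray, and ultrasound examination". Enhanced CT is "performed at 3, 6, 12, 18, 24, 32, and36 months postoperatively". CT therefore coincides with six of the nine visits; months 1, 9 and 30 have a marker test and ultrasound but no scheduled CT. The same section adds that PET, "magnetic resonance imaging, or digital subtraction angiography will be scheduled as required to investigate possible tumor recurrence". Nothing there, or in the sections on clinical evaluation and blinding, makes the primary event depend on what that imaging shows.

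Two earlier statements bear on whether laboratory values can be assumed to behave alike in the two arms. The Background says that the Pringle maneuver "will lead to I/R injury to the liver remnant, we can rationally deduce that it may harm liver function". The hypothesis section lists blood loss, transfusion, liver function and HBV load as prognostic factors and continues: "These factors may each have different, and sometimes even opposing, effects on laboratory test results". Alpha-fetoprotein is not named in either place.

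**The concern.** A time-to-recurrence comparison is only as specific as its event. If a blood value can close a patient's follow-up as a recurrence, any rise that is not caused by tumour enters the primary analysis as an event. When such events occur at the same rate in both arms, they add the same hazard to each and draw the HR towards 1. The planned power of 0.80 leaves no margin for that.

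The trial compares two techniques that the article itself expects to differ in their effect on the liver remnant. Equal marker behaviour in the two arms is therefore an assumption, not something the design guarantees. Blinding of outcome assessors would not help if the laboratory value itself differed between arms.

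**Working it through.** **Inputs from the article.** Medians 26 months (Pringle) and 36 months (non-Pringle), 249 patients per arm, power 0.80, type I error 0.05 and two-tailed tests come from the sample size section. The accrual and follow-up times come from the duration section: "main recruitment (9 months), follow-up (36 months), and analysis (6 months" months). Exponential survival and uniform accrual are assumed.

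**Step 1: reproduce the plan's figure.**
- Hazards: ln 2/26 = 0.02666 and ln 2/36 = 0.01925 per month. HR = 26/36 = 0.722.
- Event probability with 9 months of accrual and 36 further months: p = 1 − [exp(−36λ) − exp(−45λ)]/(9λ), which gives 0.659 (Pringle) and 0.541 (non-Pringle).
- Expected events: 249 × (0.659 + 0.541) ≈ 299.
- Power (Schoenfeld): Φ(√(299/4) × |ln 0.722| − 1.96) = Φ(2.813 − 1.960) = 0.803.

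This agrees with the stated 0.80.

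**Step 2: add non-tumour marker events, equal in both arms.** The article gives no rate, so a cumulative probability c over 36 months is assumed. The added hazard is g = −ln(1 − c)/36, and the observed HR is (0.01925 + g)/(0.02666 + g). Events and power follow as in step 1.

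| c over 36 months | g per month | HR | Expected events | Power | Patients per arm for 0.80 |
|---|---|---|---|---|---|
| 0 | 0 | 0.722 | 299 | 0.803 | 248 |
| 2% | 0.00056 | 0.728 | 303 | 0.790 | 257 |
| 5% | 0.00142 | 0.736 | 310 | 0.769 | 270 |
| 10% | 0.00293 | 0.750 | 321 | 0.733 | 294 |

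The number of events rises, but the HR moves towards 1 and the net effect is lower power.

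**Step 3: place the events at actual visits.** A log-rank simulation (20,000 runs per setting) gave power 0.800 with no such events. With an assumed 0.5% or 1% per visit at all nine visits (cumulative 1 − 0.995⁹ = 4.4% and 1 − 0.99⁹ = 8.6%), power was 0.771 and 0.740, in line with step 2. With the same per-visit rates only at months 1, 9 and 30, it was 0.793 and 0.783.

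**Step 4: what a difference between arms would do.** The HR is unchanged only if the added hazard in the non-Pringle arm is 0.722 times that in the Pringle arm. Below that ratio the HR moves away from 1; above it, towards 1. As an illustration of direction only: with c = 10% in one arm and half that hazard in the other, the HR is 0.700 if the Pringle arm has more and 0.789 if the non-Pringle arm has more.

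**Step 5: the price of requiring confirmation.** If every true recurrence in both arms were dated 1, 2 or 3 months later, the usable follow-up shortens by that amount. Expected events become 294, 290 and 285, and power 0.797, 0.791 and 0.784.

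**The case against.** The event is a diagnosed recurrence, and CT and the marker can be read as routes to that diagnosis, with cut-off, repeat testing and dating left to the full protocol. This stands in part: an article need not give a cut-off, and its absence is not the point here. But the article does state that either route suffices. A cut-off would change how often marker-only events occur, not whether they count.

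Imaging for possible recurrence is provided for, every visit has ultrasound, and month 30 is followed by CT at month 32. This stands as a reason to expect few false events. The visits without scheduled CT are not visits without liver imaging. It does not alter the definition, because no imaging result is required.

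The 26-month median comes from cited literature. If those studies also counted marker diagnoses, the planned power may already refer to the endpoint as written. This cannot be settled from the article, so the power losses rest on the opposite assumption.

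A reader might infer more: that clamping, by injuring the remnant, raises the marker and would manufacture a benefit for the non-Pringle arm. The documents do not support that. They never say that alpha-fetoprotein rises without tumour or differs by arm, and the two statements on liver function and laboratory results are general. A lasting difference between arms over 36 months would also have to follow from a single intraoperative injury; confining it to the first visits leaves little effect on the error rate. Figures for a false benefit, or for a severe loss of power, would rest on invented rates.

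**Conclusion.** The point holds as a defect in a stated rule: the primary event can be met by a marker level alone, and nothing in the article overrides this. The likely consequence is a modest dilution. For an assumed cumulative rate of 2% to 10%, equal in both arms, the HR goes from 0.722 to about 0.73–0.75 and power from 0.80 to about 0.79–0.73, with less loss if the events are confined to visits without CT. These figures assume exponential survival, a constant added hazard, and planned medians free of non-tumour marker events. Bias from a difference between arms is possible in either direction, but its existence, size and sign cannot be estimated from the documents. A marker rise that precedes a genuine recurrence affects only the event date and is not part of this concern. The point is worth correcting because the event defines the primary comparison and the correction is cheap.

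**What to change.** Define the primary event as recurrence confirmed by enhanced CT, MRI, PET, angiography or pathology, dated at the confirming examination. Ultrasound or chest x-ray alone should not confirm it: both are done at every visit and could add false positives of their own. An alpha-fetoprotein rise should only trigger confirmatory imaging. Report the present marker-or-CT definition as a sensitivity analysis.

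The cost is a change of wording and some additional triggered scans, for which the Follow-up section already provides. Some true recurrences would be dated later, and a few near the end of follow-up might be missed. If all were dated 1 month later, power would be about 0.797; if 3 months later, about 0.784. That calculation delays both arms equally and does not count recurrences that imaging never shows.

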### Trial population

Our study group includes researchers in five leading hospitals in China (Southwest Hospital, Chinese PLA General Hospital, Zhongshan Hospital, Nanjing Drum Tower Hospital, and the First Affiliated Hospital of SunYet-Sen University) located in the southwestern, northern, eastern, middle, and southern parts of China, respectively. All eligible patients from these five participating hospitals with a clinical diagnosis of HCC with infection will be enrolled. The study will include patients’ aged 18 years or older undergoing potentially curative (R0) resection, if preoperative imaging indicates that R0 resection can be undertaken both with and without the Pringle maneuver. Patients with extrahepatic disease, severe liver cirrhosis, or tumor-positive lymph nodes in the abdomen or hepatoduodenal ligament will be excluded. We anticipate that 50 eligible cases per month will be enrolled in the trial. A detailed list of all eligibility criteria follows.

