### Study design

This study is funded by the National Major Science and Technology Project of China on the prevention and treatment of infectious diseases, for human immunodeficiency virus and HBV [2008ZX10002-026]. This clinical trial is a registered [NCT00725335], prospective, intraoperatively randomized multicenter trial of patients undergoing curative resection for HCC. The patients will be stratified by center and allocated to groups by a permuted-blocks randomization protocol. The primary objective of this study is to compare the disease free-survival rates at 1, 2, and 3 years postoperatively between the two groups. We hypothesize that the long-term prognosis of patients who have undergone curative resection will be worse in the control group (Pringle maneuver) than in the experimental group (non-Pringle maneuver).

The detailed study design is shown in Figure1.

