### Sample size calculation and data analysis plan

The sample size of this trial was calculated using data from our previous experience and from the published literature. There are currently no data from randomized controlled trials showing the recurrence rate of HCC after hepatectomy without the Pringle maneuver. Most studies used the Pringle maneuver. This trial plans to have equal numbers of control and experimental subjects, and a 36-month follow-up period. The median survival time after the treatment that the control group will receive has been reported to be 26 months [24,44-50]. We anticipate a10-month difference in the median recurrence-free survival time between the experimental and control groups. If median survival times in the control and experimental groups are 26 months and 36 months, respectively, we will need to include 249 experimental subjects and 249 control subjects to be able to reject the null hypothesis that the experimental and control survival curves are equal with a probability (power) of 0.800. The Type I error probability associated with this test of the null hypothesis is 0.05.

Data for primary and secondary outcome measures will be analyzed using the SPSS statistical software package (SPSS UK Ltd., Woking, U.K.). Analysis will include standard descriptive statistics, Student’s t tests, correlation and regression, and two-way (group x time) repeated measures ANOVA to examine differences between the groups over time. Survival analysis will be performed. Statistical significance will be set at p < 0.05and all tests will be two-tailed. Subgroup stratified analysis will be performed according to tumor size, tumor encapsulation, Edmondson’s grade, HBV load, ischemic time, blood loss, and transfusion. The intention-to-treat analysis will be used for the patients whose portal triad clamping was changed due to safety reasons.

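### The sentence placing the final evaluation 1 year after the last enrolment contradicts the protocol's 3-year design; if followed, it would leave about half the needed events and about 53% power

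*Protocol article*

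**What the plan says.** The Endpoints section names the primary endpoint ("The primary trial endpoint will be tumor recurrence diagnosed by enhanced CT scan or serum alpha-fetoprotein level") and then gives two dates. One is the end of the study: "The formal end of the study will be at the end of the 3-year follow-up period of the last patient to be enrolled". The other is the analysis: "Final evaluation of the primary and secondary endpoints of the study will be performed 1 year after enrollment of the last patient".

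Other sections of the protocol article bear on the date:

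- Study design: the primary objective is to "compare the disease free-survival rates at 1, 2, and 3 years postoperatively between the two groups".
- Sample size calculation and data analysis plan: the calculation assumes 36 months of follow-up, two-sided alpha 0.05 and power 0.80. "If median survival times in the control and experimental groups are 26 months and 36 months, respectively", then "we will need to include 249 experimental subjects and 249 control subjects".
- Duration of the trial: after 6 months of protocol development and 3 of training come "main recruitment (9 months), follow-up (36 months), and analysis (6 months"), 5 years in all.
- Trial population: "We anticipate that 50 eligible cases per month will be enrolled in the trial".
- Abstract, Figure 1 caption and Follow-up: each patient is followed for 3 years.

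**The concern.** The 1-year sentence names the primary endpoint and calls the evaluation final, so it does not read as an interim or perioperative report. It is also the only sentence that dates the evaluation of the primary endpoint explicitly. The formal-end sentence does not cure this, because it dates a different event, two years later.

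Two things are at stake if the sentence is applied. Two of the three time points in the primary objective would lie beyond anyone's follow-up. The comparison of the curves would also rest on far fewer events than the sample size presumes, so a real effect of the planned size could easily be missed. If the conflict stays unresolved, the protocol does not settle when the primary comparison is made.

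**Working it through.** **Inputs.** Medians 26 and 36 months, 249 per arm, two-sided alpha 0.05 and power 0.80 (Sample size section). Recruitment 9 months (Duration section), or 498/50 = 9.96 months at the stated monthly rate (Trial population section). Assumptions not in the document: exponential survival, uniform accrual, no dropout. The Sample size section uses both survival and recurrence-free survival for its medians; they are applied here to the recurrence-based primary outcome.

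**Step 1: events needed.** HR = 26/36 = 0.722 and ln(HR) = -0.3254. By Schoenfeld, events = 4(1.960 + 0.8416)² / 0.3254² = 296.5, so 297. Freedman's formula gives 302.

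**Step 2: reproduce the plan's 249 per arm.** With hazard λ = ln 2/median, accrual over A months and F months after the last enrolment, the probability of an observed event is

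p = 1 − [exp(−λF) − exp(−λ(A+F))] / (λA).

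For A = 9 and F = 36, p = 0.659 (control) and 0.541 (experimental). Then:

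- Schoenfeld: 296.5/(0.659 + 0.541) = 247.0 per arm.
- Exponential, unpooled: (1.960 + 0.8416)² × (1/0.659 + 1/0.541) / 0.3254² = 249.4 per arm.
- Freedman: 251.3 per arm.

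The stated 249 is reproduced. Stopping every patient at exactly 36 months would need 265 to 270 per arm, which does not match. The stated size therefore fits an analysis 36 months after the last enrolment.

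**Step 3: the timetable.** 6 + 3 + 9 + 36 + 6 = 60 months, the stated 5 years. The last patient completes 36 months at month 6 + 3 + 9 + 36 = 54, leaving 6 months for analysis. The 1-year sentence would put the final evaluation at month 6 + 3 + 9 + 12 = 30.

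**Step 4: follow-up at the 1-year date.** It runs from 12 to 9 + 12 = 21 months, or to 21.96 months with 9.96 months of accrual. No patient has reached 24 or 36 months.

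**Step 5: events and power.** Power = Φ(√D × 0.3254/2 − 1.960), where D is the expected number of events, 249 × (sum of the two event probabilities).

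| Analysis date | Accrual (months) | p control | p experimental | Events | Power |
|---|---|---|---|---|---|
| 12 months after last enrolment | 9 | 0.354 | 0.271 | 155.8 | 0.528 |
| 12 months after last enrolment | 9.96 | 0.362 | 0.278 | 159.4 | 0.537 |
| 36 months after last enrolment | 9 | 0.659 | 0.541 | 298.9 | 0.803 |
| 36 months after last enrolment | 9.96 | 0.664 | 0.545 | 301.0 | 0.806 |

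For the first row, √155.8 = 12.48, 12.48 × 0.3254/2 = 2.031, 2.031 − 1.960 = 0.071, and Φ(0.071) = 0.528. Freedman's version gives 0.521. A log-rank simulation of 4,000 trials gives 0.53 at the 1-year date and 0.797 at 36 months (9-month accrual).

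**Step 6: what remains estimable at the 1-year date.** The 1-year recurrence-free proportions would be exp(−12 ln 2/26) = 72.6% and exp(−12 ln 2/36) = 79.4%. A comparison of these with 249 per arm has power of about 0.42.

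**Step 7: slower accrual.** With recruitment over 12, 18 or 24 months, the longest follow-up at the 1-year date is 24, 30 or 36 months, and power is 0.556, 0.605 or 0.647.

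**The case against.** The strongest reply is that one sentence stands against everything else in the article. The formal end, the timetable, the sample-size basis and the follow-up schedule all point to 3 years, and the sample size reproduces on that basis. The 1-year sentence then looks like a drafting slip, not a chosen design. This stands. The defect is an internal contradiction, and any loss of power is conditional on the 1-year sentence being the one applied.

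Three stronger readings are tempting, and the document does not support them:

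- *The primary question could not be answered at all.* At the 1-year date every patient has potential follow-up to 12 months, which is one of the three stated time points. The Endpoints section names recurrence without a time point, and the Sample size section states the null hypothesis as equality of the curves. A log-rank test could be run, though underpowered. Only the 2- and 3-year rates are out of reach.
- *No patient could ever reach 2 years by that date.* This follows from the planned 9 to 10 months of recruitment, which is a forecast. With slower recruitment some patients would pass 24 months, but power would still be well below 80% (Step 7).
- *The trial tests its primary endpoint twice at full alpha.* No section describes two primary analyses, and an alpha rule for an added look may sit in an analysis plan that is not shown. It is a risk only if both dates are used.

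The reply does not remove the conflict. The sentence is explicit, concerns the primary endpoint, and cannot be squared with the rest.

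**Conclusion.** The concern holds as a contradiction with a conditional consequence. The article gives two incompatible times for the final evaluation, two years apart. If the 1-year sentence governed with recruitment as planned, about 156 to 160 of the 297 needed events would be available (156/297 = 53%), power would be about 53%, and the 2- and 3-year comparisons could not be made. If the analysis follows 36 months after the last enrolment, about 299 events are expected and power is 80%.

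A reader might infer that the trial is underpowered or that its analysis date is settled at 1 year. Neither follows: the sample size is consistent with the later date, and most of the document points there.

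The figures rest on exponential survival, uniform accrual and no dropout; dropout would lower power at both dates. The 80% also counts events that early recruits have after their own 36 months and before the common analysis date. If each patient's observation stops at exactly 36 months, about 278 events are expected and power is 0.774, still far above the 1-year figure.

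**What to change.** In the Endpoints section, change the final-evaluation sentence so that the primary and secondary endpoints are evaluated after the last randomised patient has completed 36 months of follow-up. This agrees with the formal end of study, the primary objective, the sample-size basis and the timetable.

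If the sponsor also wants a 1-year evaluation of recurrence or survival, label it interim and state how alpha is handled. Whether to have such a look is the sponsor's choice; only the reconciliation of the dates is required.

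The cost is one sentence, plus an alpha rule if the 1-year look is kept. The 36 months of follow-up and the 6 months of analysis are already in the 5-year timetable, and no more patients are needed.
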